#### Quantitative analysis of the implementation component of the trial

Similar to the effectiveness aspect of the trial, we will compare the pre- and post-intervention rates of patients’ insurance coverage and receipt of recommended cancer screenings using DID generalized linear/non-linear mixed models comparing Arm I and Arm II. Moreover, post-implementation, we will assess and compare use of the tools across the study arms, including information such as who uses which tools and functions, as well as frequency and timing of use. This will help identify individual- and clinic-level factors associated with more frequent use of the health insurance support HIT tools.

To evaluate tool use, we will assess monthly data (e.g., percent of patient charts with evidence of tool use) in regression models to estimate associations between use and patient panel characteristics. Additionally, we will describe and compare the characteristics of patient encounters with tool use vs. those with no tool use, via random-effect logistic regression models that assess associations between use of the insurance support HIT tools (dependent variables) and socio-demographic characteristics (independent variables) and other possible confounders.

#### Qualitative analysis

Our team will meet regularly to review transcripts and field notes. We will also listen to and discuss key segments of the audio-recorded interviews. This step is crucial to monitoring data quality, refining the observation and interview guides, making sampling decisions, and monitoring theme saturation. This ongoing process will be used to track emerging themes and to create a coding template for more in-depth analysis. We will follow the 5-phase analysis strategy described by Miller and Crabtree (describing, organizing, connecting, corroborating/legitimizing, representing) [50, 51]. To accomplish these steps, we will use an immersion-crystallization approach in which the team reads and discusses the data for each clinic (immersion) to identify key findings (crystallization) [52, 51]. We will do this two times: first, to identify key themes within each case (clinic) and second, to identify cross-case finding. A key step in this process is the connecting phase where we will connect what we are seeing in the qualitative data with the data usage patterns from the EHR, as well as with quantitative data.

## Discussion

Recent policies have created new opportunities for CHC patients to obtain health insurance coverage. However, research indicates that simply making insurance available is not enough to improve rates of continuous coverage; outreach efforts are needed to keep eligible patients insured [53–60]. Multi-strategy approaches have shown early promise in improving enrollment and retention of eligible children in public health insurance programs, but few technological solutions have been tested in primary care settings or with populations of adults eligible for Medicaid coverage [61, 62]. With the passage of the ACA, CHC patients in states that expanded Medicaid now have better access to insurance coverage. Medicaid enrollment increased by 12.9 % in expansion states and by 2.6 % in non-expansion states [63].

The growth of HIT infrastructure in CHCs has created new opportunities for building tools capable of supporting health insurance enrollment and retention. While clinic-based HIT tools (e.g., registries, “pop-up” alerts, automated e-mails to patients) have proven effective at enhancing chronic disease management [64], we know of no previous studies to test the use of similar mechanisms to connect adult patients to Medicaid coverage with the aim of improving insurance coverage continuity and cancer screening rates. Therefore, this study will test the effectiveness of these tools and compare different strategies for supporting their implementation in “real-world” practice settings.

This protocol has several limitations. First, a participant site could withdraw from the study; however, the large number (>300) of OCHIN member CHCs could provide substitute sites. Second, as with any study conducted in “real-world” settings, unobserved changes will undoubtedly occur over time in a non-random fashion within the study environments (e.g., community health insurance outreach efforts). We acknowledge that these unexpected occurrences may make it difficult to isolate the effect of the health insurance support HIT tools and the implementation support strategies in this pragmatic trial. To address this, our approach uses both clinic- and individual-level comparisons. Further, the implementation component of this trial is strengthened by the use of a two-arm cluster-randomized design, and the tool effectiveness component uses a propensity score-matched control group of clinics to adjust for temporal trend. Third, while EHR data sources are not developed for research purposes, we have conducted multiple validation studies and have successfully built research datasets in the past [31–69]. Finally, as with most implementation research, there are questions about sustainability. Conducting this work in partnership with OCHIN positions us to sustain the aspects of the insurance support HIT tools proven effective. OCHIN is committed to maintaining the tools and will also enable rapid dissemination to more CHCs.

Despite these limitations, this study has great potential impact, given the central role played by CHCs in providing health care to vulnerable populations and the expansion of both CHCs and public health insurance coverage for adults as supported by the American Recovery and Reinvestment Act and the ACA [70]. Indeed, as health insurance expansions continue, it becomes increasingly important to know about effective methods for connecting patients to coverage. The proposed study will contribute to this knowledge gap. We believe our findings will have broad relevance to public health and healthcare reform efforts. We will work with our community partners and state policymakers to widely distribute findings and plan for widespread dissemination of the insurance support HIT tools, if proven effective. Further, the insurance support HIT tools have the potential to facilitate access to a wide range of recommended healthcare services beyond cancer screening and prevention.

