### Study setting and population

The study will be carried out at OCHIN, a non-profit 501(c)(3) collaborative that was created in 2001 to develop HIT tools for CHCs. Originally called the Oregon Community Health Information Network, OCHIN has 81 health system members in 17 states with 376 clinics and 6322 providers caring for nearly 2,000,000 patients.

OCHIN provides and maintains a comprehensive electronic health information infrastructure, built on software from Epic© Systems. The OCHIN EHR is linked across all member clinics through an Organized Health Care Arrangement, which gives clinics a fully integrated EHR in which each patient has a single medical record. There is one enterprise-wide master patient index; health record data “follow the patient” to any OCHIN clinic.

The Institutional Review Board of the Oregon Health & Science University has reviewed and approved this study. The study is registered with ClinicalTrials.gov (#NCT02355262).

*Inclusion criteria for intervention and control sites*. Study sites were required to be primary care clinics that implemented the OCHIN EHR prior to January 1, 2013, have >1000 adult patients with ≥1 visits in the past year, and be located in a state that expanded Medicaid in 2014 [42].

*Inclusion criteria for patients*. All patients (ages 18–64) with at least one encounter at a CHC in OCHIN since January 1, 2013 (*n* ≈ 1,000,000 adults), will be included in the study dataset for quantitative analysis. As very different insurance products are available to children <18 and patients >64 years of age, these age groups are excluded. All study sites serve low-income, ethnically diverse populations with lower rates of cancer screening (see Table 1) and higher rates of publicly insured and uninsured patients, compared to national rates [43].

**Table 1 Tab1:** Insurance coverage and cancer screening rates in the US population and OCHIN

	US population, 2010 (%)	OCHIN, 2014 (%)
Insurance coverage		
Private	64.2	17.6
Public	34.3	48.4
None	13.4	34.0
Cancer screening among insured patients		
Cervical	83.0	36.5
Colorectal	58.6	42.8
Breast	72.4	60.3
Cancer screening among uninsured patients		
Cervical	63.8	27.0
Colorectal	20.7	19.9
Breast	38.2	39.3

Source for US population: Census [71], CDC [72]; source for OCHIN population: OCHIN EHR data

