### Overview of implementation component of trial

#### Intervention sites

An OCHIN team member identified 99 clinics in 32 eligible health center organizations within OCHIN. Of those invited, 23 clinics in 7 health center organizations agreed to participate (23 % of eligible clinics) and 76 clinics in 25 organizations declined (77 % of eligible clinics). The 7 participating organizations are located in 3 Medicaid expansion states (Oregon, California, and Ohio). These organizations varied in size; the number of primary care clinic sites per organization ranged from 1 to 6. Due to the possible correlation among clinic sites in the same organization, an independent biostatistician randomized the 23 clinics by service organization. A covariate-constrained cluster randomization [44] was used to balance the number of clinics between the two treatment arms. The randomization was balanced using the following covariates: state the organization was located in (Oregon vs. non-Oregon), total number of patients per organization, and percentage of uninsured patients per organization. The biostatistician and research team members were blind to the clinics during randomization. Once randomized, the study team was given the list of clinics participating in each study arm (11 in Arm I and 12 in Arm II).

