### Trial status

The recruitment and randomization into the study arms have been completed. We also identified the control group using the propensity-matched score method. The implementation of the health insurance support HIT tools is scheduled for Fall 2015.

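### Substitution from more than 300 OCHIN clinics, the article's answer to site withdrawal, rests on membership rather than eligibility; if used, it would add unrandomised and unmatched intervention sites

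*Protocol article*

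**What the plan says.** The first limitation in the protocol article's Discussion is that "a participant site could withdraw from the study; however, the large number (>300) of OCHIN member CHCs could provide substitute sites". This is the only response to withdrawal that the article gives.

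Other sections bear on whether it could work:

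- **Study setting and population** gives the size of the network: "OCHIN has 81 health system members in 17 states with 376 clinics". It then sets one list of criteria for both groups of clinics: "Study sites were required to be primary care clinics that implemented the OCHIN EHR prior to January 1, 2013, have >1000 adult patients". A further condition is that the state expanded Medicaid in 2014.
- **Intervention sites** says that an OCHIN team member "identified 99 clinics in 32 eligible health center organizations within OCHIN". Of these, 23 clinics in 7 organizations agreed and "76 clinics in 25 organizations declined". The 7 organizations were randomised by a covariate-constrained method, balancing state, patient numbers and percentage uninsured. The team then received the arm list (11 clinics in Arm I, 12 in Arm II).
- **Overview of effectiveness component** says that 23 control clinics were matched 1:1 to the intervention clinics from a pool of 64.
- **Trial status** confirms: "The recruitment and randomization into the study arms have been completed". It adds that the control group has been identified.

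**The concern.** There are two linked problems.

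First, the reassurance rests on the wrong count. Belonging to OCHIN does not make a clinic eligible, and the article's own recruitment figures show that every eligible clinic has already given its answer. A substitute would have to be a clinic that refused, or one that was not on the eligible list.

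Second, a substitute added now would not belong to the design. The randomised comparison rests on 7 organizations allocated together under a balance constraint. The effectiveness comparison rests on controls chosen to resemble 23 particular clinics. A clinic added later has neither property. Its arm would be that of the site it replaced, and the team would know that arm when choosing it. The same limitations paragraph goes on to cite the cluster-randomised design and the matched controls as the study's protections, and substitution would weaken both.

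Withdrawal may be related to difficulty with the tools, and a replacement must by definition be willing. That is the route by which bias could enter.

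**Working it through.** **1. Reproduce the recruitment count (Intervention sites).**

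- Clinics: 23 + 76 = 99, as stated.
- Organizations: 7 + 25 = 32, as stated.
- Percentages: 23/99 = 23.2% and 76/99 = 76.8%, matching the printed 23% and 77%.

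**2. Count what is left.**

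- Eligible clinics that have neither agreed nor declined: 99 − 23 − 76 = 0.
- Eligible organizations in the same position: 32 − 7 − 25 = 0.

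**3. Compare with the pool that the Discussion offers.**

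- The figure of more than 300 agrees with the 376 clinics in the network.
- Eligible share: 99/376 = 26%.
- Not on the eligible list: 376 − 99 = 277.

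**4. Set the design steps against a substitution.**

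| Design step, already completed | Position of a substitute intervention clinic |
|---|---|
| 7 organizations randomised as one set | Not in the set; if from another organization, a new unrandomised cluster |
| Allocation constrained on state, patient numbers and percentage uninsured | Outside the constraint |
| Arm list released to the study team | Added with allocation known |
| 23 controls matched 1:1 to the 23 recruited clinics | Has no matched control |

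**5. Size if one organization were lost and replaced.**

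- Randomised units affected: 1/7 = 14%.
- Organizations have 1 to 6 clinic sites. For one with 6: 6/23 = 26% of intervention clinics, and 6/11 = 55% of Arm I or 6/12 = 50% of Arm II.

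**6. Direction of any bias.**

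- *Arm I versus Arm II:* both arms receive the tools. Replacing struggling Arm I clinics with willing ones raises Arm I and shrinks an Arm II advantage; doing so in Arm II enlarges it. The sign depends on which arm loses sites.
- *Intervention versus matched controls:* replacing struggling clinics with willing ones in either arm raises the intervention group, so the probable direction favours the tools.

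**7. Control clinics.** The pool holds 64 − 23 = 41 unselected clinics. Replacing a control by re-matching would leave the randomisation untouched. However, Trial design uses the term participating clinics for the intervention group, so the Discussion's sentence is most naturally read as covering intervention sites.

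**The case against.** The strongest reply is that this is one sentence in a limitations paragraph, and it says only that substitutes could be provided. The Methods contain no replacement procedure and do not say that a withdrawn site leaves the analysis. No estimate, sample size or model depends on the sentence. Harm requires that a site withdraws, is replaced, and that the replacement enters the comparison. The figure is also correct as a count of members, and clinics that declined could be asked again. All of this stands, and it limits the point to a contingency that should not be used. It does not rescue the sentence, which remains the article's only stated remedy.

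Four stronger readings are tempting, but the article does not support them:

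- *A settled plan that breaks the randomisation.* The wording is conditional, and nothing is damaged unless a substitution is made.
- *Bias towards benefit in both comparisons.* For Arm I versus Arm II the direction is not determined.
- *The controls are the clinics that declined.* The eligibility criteria are common to both groups, so overlap is likely, but the article never links the 64 control-eligible clinics to the 76 that declined.
- *Withdrawal costs nothing because outcomes come from the EHR.* The article does not promise EHR access after withdrawal; a site might leave OCHIN or refuse use of its data. User perceptions, interviews and site visits are not EHR outcomes.

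It is also fair to say that detailed handling of withdrawn clusters may sit in a full protocol or analysis plan that is not shown. The absence of such detail is not the point made here. The point is the remedy that the article does state.

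**Conclusion.** The point holds as a flaw in a stated contingency. The pool of more than 300 is a membership count; by the article's own figures, no eligible clinic remains that has not already answered. A substitute intervention clinic would be unrandomised, unmatched, outside the covariate balance and added with allocation known. With 7 randomised units, even one replacement is material: 14% of units and up to 26% of intervention clinics. It could bias Arm I versus Arm II in a direction that depends on which arm loses sites, and would probably favour the tools against the matched controls.

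This rests on three assumptions: that the Discussion means intervention sites, that the list of 99 is complete under the stated criteria, and, for the direction of bias, that withdrawal is related to difficulty with the tools. The counts themselves need no assumption.

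**What to change.** - Remove substitution as a remedy for intervention sites.
- State that a withdrawn clinic or organization is analysed in its assigned arm, from OCHIN EHR and Medicaid data over the 18-month post-intervention period, wherever those data remain available and their use is permitted. Retain its matched controls.
- State that any site added later is excluded from the randomised comparison and reported only descriptively or in a sensitivity analysis.
- Replace the figure of more than 300 with the facts: 99 clinics were eligible, and all have already agreed or declined. The 99 should not be presented as a remaining pool.

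The text change is small and best made before the tools are implemented in Fall 2015. It has two real costs. Keeping withdrawn clinics in their arm dilutes the effect, and not trivially if an organization with 6 of the 23 clinics leaves. Survey, interview and site-visit outcomes may also be missing for withdrawn sites, and EHR data cannot fill that gap.

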### Trial status

The recruitment and randomization into the study arms have been completed. We also identified the control group using the propensity-matched score method. The implementation of the health insurance support HIT tools is scheduled for Fall 2015.

## Abbreviations

ACA: Affordable Care Act
CHC: community health center
DID: difference-in-differences
EHR: electronic health record
FOBT: fecal occult blood test
HIT: health information technology
HPV: human papillomavirus
LMS: learning management system
